# Postoperative drainage for 6, 12, or 24 h after burr-hole evacuation of chronic subdural hematoma in symptomatic patients (DRAIN-TIME 2): study protocol for a nationwide randomized controlled trial

**DOI:** 10.1186/s13063-022-06150-x

**Published:** 2022-03-14

**Keywords:** Chronic subdural hematoma, Neurosurgery, Neurology, Drain, Randomized control trial, Recurrent chronic subdural hematoma

## Abstract

**Background:**

Chronic subdural hematoma (CSDH) is a common acute or subacute neurosurgical condition, typically treated by burr-hole evacuation and drainage. Recurrent CSDH occurs in 5–20% of cases and requires reoperation in symptomatic patients, sometimes repeatedly. Postoperative subdural drainage of maximal 48 h is effective in reducing recurrent hematomas. However, the shortest possible drainage time without increasing the recurrence rate is unknown.

**Methods:**

DRAIN-TIME 2 is a Danish multi-center, randomized controlled trial of postoperative drainage time including all four neurosurgical departments in Denmark. Both incapacitated and mentally competent patients are enrolled. Patients older than 18 years, free of other intracranial pathologies or history of previous brain surgery, are recruited at the time of admission or no later than 6 h after surgery. Each patient is randomized to either 6, 12, or 24 h of passive subdural drainage following single burr-hole evacuation of a CSDH. Mentally competent patients are asked to complete the SF-36 questionnaire. The primary endpoint is CSDH recurrence rate at 90 days. Secondary outcome measures include SF-36 at 90 days, length of hospital stay, drain-related complications, and complications related to immobilization and mortality.

**Discussion:**

This multi-center trial will provide evidence regarding the shortest possible drainage time without increasing the recurrence rate. The potential impact of this study is significant as we believe that a shorter drainage period may be associated with fewer drain-related complications, fewer complications related to immobilization, and shorter hospital stays—thus reducing the overall health service burden from this condition. The expected benefits for patients’ lives and health costs will increase as the CSDH patient population grows.

**Trial registration:**

ISRCTN Registry ISRCTN15186366. Registered in December 2020 and updated in October 2021. This protocol was developed in accordance with the SPIRIT Checklist and by use of the structured study protocol template provided by BMC Trials.

**Supplementary Information:**

The online version contains supplementary material available at 10.1186/s13063-022-06150-x.

## Introduction

### Background and rationale {6a}

Chronic subdural hematoma (CSDH) is one of the most common neurosurgical conditions, especially in older patients, and causes serious morbidity and mortality [1]. It consists of a collection of partly or totally liquefied old blood on the brain’s surface between the dura mater and arachnoid [2]. The exact pathogenesis of CSDH remains unclear, but head trauma is known to be an important factor. CSDH can develop following only a minor injury to the head but also in the absence of a known trauma [1]. Symptoms of CSDH depend upon the size of the hematoma and specific location and may include headache, focal neurological deficits, speech problems, gait disturbance, falls, cognitive decline, confusion, and decreased consciousness. Patients with significant symptoms are admitted to a neurosurgical department for operative treatment. Burr-hole evacuation is the standard procedure in most centers. However, recurrence of CSDH is observed in 5–20% of patients, requiring readmission and further surgery. Although it is still debated whether to use subperiosteal versus subdural drain [3], there is evidence that postoperative drainage is effective in reducing the symptomatic recurrence of CSDH [4]. The shortest possible postoperative drainage period without compromising the drainage effect is preferable, both from a medical and a health economic perspective. It has been shown to be much more advantageous to remove the drain at 48 h compared to 96 h as the rate of morbidities was significantly decreased [5]. Unpublished data from a newly terminated Danish multi-center, randomized controlled trial (DRAIN-TIME 1) of postoperative drainage time could not show 48 h drainage to be superior to 24 h regarding the recurrence rate or death at 3 months.

DRAIN-TIME 2 is a nationwide, multi-center, randomized controlled trial investigating the shortest possible subdural drainage time without significantly increasing the recurrence rate. Patients will be randomized to a postoperative drainage period of 6, 12, or 24 h. The potential impact of this study is significant as we believe that a shorter drainage period may be associated with fewer drain-related complications, fewer complications related to immobilization, and shorter hospital stays.

#### Trial rationale

We hypothesize that a drainage period of 6 and/or 12 h is non-inferior to 24 h of drainage regarding recurrence rate, and we hypothesize that the shortest possible drainage time is associated with fewer drain-related complications, faster mobilization, and shorter hospital stays.

### Objectives {7}

#### Primary objective

The primary objective is to investigate if the drainage period of 6 and**/**or 12 h is non-inferior to 24 h of drainage regarding CSDH recurrence rate at 3 months.

#### Secondary objectives

The following are the secondary objectives:
Compare the long-term (90 days) outcome measuresCompare the drain- and immobilization-related complicationsCompare the length of hospital stay (at the department of neurosurgery)

#### Exploratory (mechanistic) objective (sub-study)

The exploratory objective is to assess the composition of proteomics, inflammatory, and angiogenetic markers in the blood, CSDH fluid, surrounding membranous tissue, and draining fluid.

### Trial design {8}

The DRAIN-TIME 2 study is a Danish multi-center, national randomized controlled non-inferiority trial with three parallel arms. The arms correspond to 6, 12, and 24 h of drainage, where the former two arms are experimental and the 24 h group is the common control arm. Online randomization with a 1:1:1 allocation will be performed.

The trial uses a multi-arm, multi-stage (MAMS) design, which enables adaptive reductions of the number of experimental arms considered during the trial, with the aim to lower the required sample size on average. The applied design is described in Bratton et al. [6]. Our trial is organized into five stages. After each stage, non-inferiority of both arms is tested during an interim analysis at stage-specific significance levels. Significant arms continue to the next stage, whereas non-significant arms can be dropped (non-binding).

The final non-inferiority test decision is taken after the final stage (or as soon as both experimental arms are stopped) and uses all available data. Interim and final analyses rely on the same primary outcome and the same non-inferiority margin.

## Methods: participants, interventions, and outcomes

### Study setting {9}

This study is performed by the Danish Chronic Subdural Hematoma Study group (DACSUHS), which is a national steering committee with participants from all neurosurgical departments in Denmark. DACSUHS coordinates CSDH management and research in Denmark. All study sites are thus in Denmark, and all Danish neurosurgical departments are participating. There are no private facilities for cranial neurosurgery in Denmark. Patients are admitted to their local neurosurgical department after a computed tomography (CT) has confirmed the diagnosis. Local clinical neurosurgical teams review the patients upon admission and will assess the eligibility for the DRAIN-TIME 2 study. The decision for surgery is made on an individual basis by the neurosurgical teams together with the patient (if possible) and their family. The study was approved on two levels by the Danish Regional Committees on Health Research Ethics, so both incapacitated and mentally competent patients can be enrolled.

### Handling anti-coagulant therapy

Preoperative management (pause) of anti-coagulant therapy was performed in accordance with the recommendations of the Danish Society for Hemostasis and Thrombosis, published in 2016 (https://www.dsth.dk/pdf/PRAB_2016_WEB.pdf). There is no solid evidence regarding the time of restart of anti-coagulant treatment post-surgery, in order to minimize the risk of recurrence on the one hand and prevent thromboembolic complications on the other hand. Therefore, DACSUHS made a consensus decision regarding the restart of treatment: Anti-coagulant medication can be resumed 14 days after surgery (7 days if patients receive low-molecular-weight heparin, as recommended by the Danish Society for Hemostasis and Thrombosis for certain high-risk patient categories). All patients who receive anti-coagulant treatment for atrial fibrillation are referred to the department of cardiology at the time of discharge, in order to determine whether they are candidates for atrial ablation, so that anti-coagulant therapy can be avoided.

### Public and/or patient involvement in designing the study protocol

The study protocol was designed by DACSUHS. This study builds on the results from the DRAIN-TIME 1 study, solely focusing on drainage time post-surgery. All other patient care is the standard treatment. Therefore, we have considered any public and/or patient involvement unfruitful in the process of designing the present study protocol.

### Eligibility criteria {10}

Screening of patients to determine eligibility for participation in the study will be performed by the neurosurgical team upon admission according to the following criteria.

#### Inclusion criteria

The following are the inclusion criteria:
Adult patients (≥ 18 years).Minimum 2 weeks’ time span from known head trauma.Patients with symptomatic CSDH confirmed on CT or magnetic resonance imaging (MRI), admitted to a neurosurgical department for operative treatment.Patients undergoing a single burr-hole evacuation and placement of a passive subdural drain.All patients independent of GCS at admission can be included.

#### Exclusion criteria

The following are the exclusion criteria:
Patients with known abnormalities in their cerebrospinal fluid (protein and glucose levels, cell count, and type)Patients with changes or abnormalities in their normal cerebrospinal fluid dynamics, e.g., obstructive hydrocephalus, normal pressure hydrocephalus, intracranial hypotension, and ventricular peritoneal shuntPatients with additional/previously intracranial pathology that requires/has required neurosurgical treatment (e.g., brain tumor, vascular malformation, abscess)Patients with recurrent CSDH or with previous craniotomy or other transcranial surgery (for any reason)

### Who will take informed consent? {26a}

Informed consent will be obtained by a member of the research team upon admission or immediately after surgery. The Danish confidentiality law requires that the patient and any relatives are orally informed about the trial, including its rationale and overall purpose. Written patient information and the consent form will also be handed out and reviewed together with the patient. Both oral and written consent must be obtained from the patient before study randomization. The patients will be made aware of the right to a reflection period and that they can withdraw their consent at any stage. Patients who do not wish to take part in the trial will have a postoperative drainage period of 24 h, which is the current standard treatment in Denmark.

At Odense University Hospital and Rigshospitalet, we will perform an exploratory/mechanistic sub-study. Patients will be given additional patient information and an additional consent form so that they can consider whether they would like to take part in the sub-study.

Patients who are temporarily incapacitated due to severe symptoms can still be enrolled in the trial if oral and written consent is obtained from both A and B (see below) no later than 6 h post-surgery:
A)The patient’s legal representative. If at any stage the patient’s legal representative chooses to withhold or withdraw the consent, the patient will be excluded from the trial.B)A healthcare professional (medical doctor) who is independent of the interests of the persons responsible for the trial and of interests in the project in general. The consent may initially be oral, and the doctor’s first and last name must be noted in the medical record.

The patient can then be randomized.

Mentally incapacitated patients relinquish the authority, that is the competent patients’ right, to choose among professionally acceptable alternative treatments or to participate in research projects. While standards to determine intellectual capacity remain unclear, a practical approach is to demonstrate that a patient is able to describe the physician’s view of the situation and to understand the physician’s opinion as to the best intervention [7]. We consider patients to be incapacitated if they are unable to participate in the medical examination; are not aware of the time, place, and personal information; or are somnolent or comatose.

Patients who regain capacity post-surgery will be informed about the clinical trial, and consent will be sought. In most cases, this will happen during the stay at the department of neurosurgery. If this is not the case, evaluation of capacity will be performed at 90 days follow-up.

All patients admitted to the neurosurgical departments will receive standard care and will be monitored pre- and postoperatively as per routine clinical practice. Patients will either be discharged to home or transferred to another department or hospital. The Short-Form 36 (SF-36) questionnaire will be used for the 90 days follow-up and will be handed out to patients before discharge. In addition, the patient will receive the questionnaire by mail after 90 days. A member of the research team will contact the patient or the patient’s legal representative by telephone in order to determine their capacity, obtain a Modified Rankin Scale score, and guide the patient through the SF-36 questionnaire. If the patient is considered to be incapacitated, then the patient will be deemed as lost to follow-up concerning SF-36.

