#### Secondary outcome measures

The following are the secondary outcome measures:
Mortality rate at 90 days.Cause of death (e.g., related to recurrence, a symptomatic complication post-surgery comorbidities).Modified Rankin Scale at 90 days (Table 1).Patient-reported health status assessed by the SF-36 questionnaire (during admission and at 90 days follow-up).Length of hospital stay (at the department of neurosurgery before discharge to home or transfer to another hospital).Complications related to the drain such as bleeding from the skin, pain, general discomfort, and infection will be monitored as long as the patients are admitted to the neurosurgical department, and therefore, the observation period can vary. Drain-related complications are not to be graded regarding severity, but as “yes or no.” Time (hours) of the onset of symptoms post-surgery will also be noted.Complications related to immobilization such as deep venous thrombosis and/or pulmonary embolism and brain infarction will be monitored as long as the patients are admitted to the neurosurgical department, and therefore, the observation period can vary. These complications will be noted as “symptomatic” or “asymptomatic.” The time (hours) of the onset of symptoms post-surgery will also be noted.Sub-analyses of patients with recurrence at 90 days: co-morbidities, medications, age, gender, and evaluation of hematoma subtypes on CT from admission (homogenous, separated, mixed, or membranous [2]).

**Table 1 Tab1:** Modified Rankin Scale (mRS)

mRS score	Description
0	No symptoms
1	No significant disability despite symptoms; able to carry out all usual duties and activities
2	Slight disability; unable to carry out all previous activities but able to look after own affairs without assistance
3	Moderate disability: requiring some help (e.g., with shopping/managing affairs) but able to walk without assistance
4	Moderately severe disability: unable to walk without assistance and unable to attend to own bodily needs without assistance
5	Severe disability; bedridden, incontinent, and requiring constant nursing care and attention
6	Dead

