### Methods in analysis to handle protocol non-adherence and any statistical methods to handle missing data {20c}

Loss to follow-up is expected to be rare, and analyses will be done as complete case analyses. All outcomes will be analyzed using intention-to-treat analyses. For the primary outcome, this will be supplemented by an as-treated sensitivity analysis in which the observed drainage times will be used as a continuous covariate instead of the randomly assigned drainage times.

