The strengths of this study are that it includes the whole country (all neurosurgical departments in Denmark) and that all patients older than 18 years can be included, including incapacitated patients. The latter group is poorly studied, often limited by the lack of ethical permission, but is particularly interesting as they are the patients who are often in the worst medical condition. We can only speculate whether this group of patients will differ from the others in terms of the effect of the three drainage arms. As this study is conducted in Denmark only, it can also be questioned how applicable the results will be to other populations. However, looking at European Statistics 2020 (EUROSTAT) regarding the population structure and aging, Denmark is “average” compared to the other European countries, and therefore, we believe the results will still be widely applicable [23].

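### The 90-day SF-36 comparison is labelled intention-to-treat with rare loss, but by the protocol's own rule it is made only among survivors with capacity

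*Protocol article*

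**What the plan says.** All places are in the protocol article.

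- **Who is enrolled.** The abstract (Methods) says: "Both incapacitated and mentally competent patients are enrolled". The Discussion counts it as a strength that "all patients older than 18 years can be included, including incapacitated patients".
- **Who answers the SF-36.** The abstract adds: "Mentally competent patients are asked to complete the SF-36 questionnaire". The secondary outcome is "Patient-reported health status assessed by the SF-36 questionnaire (during admission and at 90 days follow-up").
- **What happens at 90 days.** Section {26a} deals with patients who have not regained capacity during the stay: "If this is not the case, evaluation of capacity will be performed at 90 days follow-up". It then fixes the consequence: "If the patient is considered to be incapacitated, then the patient will be deemed as lost to follow-up concerning SF-36".
- **How it is analysed.** Section {20a}, Secondary outcomes, names linear or ordinal regression for SF-36. Each shorter-drainage arm is tested for superiority over 24 h, two-sided at 0.05.
- **Missing data.** Section {20c} states: "Loss to follow-up is expected to be rare, and analyses will be done as complete case analyses". It continues: "All outcomes will be analyzed using intention-to-treat analyses". The only sensitivity analysis named there is an as-treated one for the primary outcome.

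**The concern.** Section {20c} rests complete-case analysis on loss being rare and does not distinguish between outcomes. For SF-36 the protocol itself creates a further loss that has nothing to do with failure to trace patients. Everyone judged incapacitated at the 90-day contact is removed by rule, and everyone who has died is removed by the nature of the instrument. Both are states that arise or persist after randomisation, and both go with a poor course.

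The arms that remain are no longer the randomised arms, so the intention-to-treat label does not fit. If one drainage time left more patients dead or incapacitated, that arm would contribute fewer of its poor outcomes to the SF-36 comparison. Its quality of life could then look more favourable than it was. The Discussion intends to draw on SF-36 for quality of life, so readers need to know which population the result describes.

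**Working it through.** The protocol gives no expected SF-36 loss, sample size or power for SF-36, so there is no figure of its own to reproduce. The main check is on the text; the arithmetic after it is illustration.

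**1. Outcomes side by side**

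| Outcome | Source at 90 days | Incapacitated patients | Patients who died |
|---|---|---|---|
| Recurrence | medical record ({18a}, {18b}) | covered | record can be reviewed |
| Mortality | medical record ({18a}) | covered | is the event |
| mRS | telephone contact with patient or legal representative ({26a}) | covered | level 6 (Table 1) |
| SF-36 | patient only ({26a}) | removed by rule | no score, no handling stated |

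The rare-loss premise is plausible for the first three rows. It does not cover the fourth. No section gives a proxy SF-36, a value or rank for incapacity or death, or an SF-36 sensitivity analysis. Section {18b} offers a clinic visit when a telephone assessment is not valid, but this does not lift the rule in {26a}.

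**2. How a bias would arise**

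Let q be the share incapacitated in an arm, and let those patients score D points below patients with capacity, who score alike in both arms with mean m. The mean over all living patients is (1 − q)·m + q·(m − D) = m − D·q. The true difference, experimental minus control, is −D·(qE − qC). The complete-case difference is 0. The hidden difference is therefore D·(qE − qC). This holds for living patients only, since a dead patient has no SF-36 value to restore.

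D and the excess qE − qC are both pure assumptions:

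| D (points) | excess 0 | excess 2 pp | excess 5 pp | excess 10 pp |
|---|---|---|---|---|
| 10 | 0 | 0.2 | 0.5 | 1.0 |
| 20 | 0 | 0.4 | 1.0 | 2.0 |
| 30 | 0 | 0.6 | 1.5 | 3.0 |

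With equal shares the between-arm bias in this model is zero. The mean level is still overstated by D·q, for example 20 × 0.10 = 2 points in each arm.

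**3. Scale against sampling error**

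The sample size table gives at most 724 per arm, for arms reaching stage 5. If 10% or 20% have no score (assumed), 72 or 145 drop out and 652 or 579 remain. With an assumed SD of 25, SE = 25·√(2/n):

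- n = 652: 25 × √(2/652) = 1.38
- n = 579: 25 × √(2/579) = 1.47

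A hidden 1.5 points, which needs the largest assumed deficit and a 5-point excess, is thus about one standard error.

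**4. A second model**

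Take a normal score with SD 10 and remove everyone below a common threshold: 10% of control and 15% of the experimental arm. The true difference is 10 × (z₀.₁₀ − z₀.₁₅) = 10 × (−1.282 + 1.036) ≈ −2.45. Truncation raises each mean by 10·φ(z_q)/(1 − q), which is 1.95 for control and 2.74 for experimental. The complete-case difference is −2.45 + (2.74 − 1.95) = −1.66. Here the rule shrinks a real difference and does not erase it. The result depends on the model chosen, so it gives no estimate for this trial.

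**The case against.** The strongest reply is that the patients in question are not lost to the trial. At the same 90-day contact the mRS can be obtained through the legal representative, death is its level 6, and mortality is a separate secondary outcome. An arm that left more patients dead or disabled would show it there. This stands, and it confines the flaw to SF-36.

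Second, the restriction is disclosed. The abstract says that competent patients complete the SF-36, and a self-report instrument cannot be answered by someone who is somnolent or disoriented. This also stands as to measurement. It does not justify calling the analysis intention-to-treat or resting it on rare loss.

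Third, a reader might infer from the enrolment of incapacitated patients that a large share will be missing at 90 days. A reader might also cite the earlier trial, which recruited 21 of 37 operated patients per month when only patients able to consent were eligible. The documents do not support that inference. Section {26a} describes incapacity at entry as temporary. The remaining 16/37 = 43% were not recruited for any reason, refusal included, and the figure says nothing about capacity at 90 days. The Discussion's remark that incapacitated patients are often the sickest also concerns patients at inclusion.

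Fourth, counts of missing questionnaires and sensitivity analyses for a secondary outcome often belong in a statistical analysis plan, which is not at hand. That is fair for the detail. The point here is a rule the protocol does state, with a justification that does not fit one of the outcomes it covers.

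**Conclusion.** The concern holds in a limited form. Sections {26a} and {20c} do not fit together for SF-36: the loss is planned, is not random and depends on a state after randomisation, so the comparison is among survivors with capacity. It can be biased if death or incapacity differs between arms.

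Size and direction cannot be derived from the document. The 0 to 3.0 points in the table rest wholly on assumed deficits and imbalances, and nothing in the document shows that an imbalance is likely. A reader might infer that the trial as a whole loses sight of its worst outcomes, or that the SF-36 result will be misleading. Neither follows, because mRS and mortality include these patients and recurrence comes from the medical record. This is a low-cost improvement to one secondary outcome and does not threaten the primary conclusion.

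**What to change.** 1. In {20a} and {20c}, state that the complete-case SF-36 result applies to patients alive and with capacity at 90 days and is not an intention-to-treat comparison. Keep the analysis itself.
2. In {20c}, limit the rare-loss justification to outcomes taken from the medical record or obtainable by proxy.
3. Add one SF-36 sensitivity analysis by ordinal (rank-based) regression, with dead and incapacitated patients in the lowest categories and the remaining patients ranked by score. Questionnaires missing for other reasons should not be placed there.
4. Report the number of missing SF-36 questionnaires by arm and reason (death, incapacity, other), and interpret SF-36 together with mRS and mortality.

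The cost is one additional analysis and some wording. Ordinal regression is already named in {20a}, and death and capacity are already determined at follow-up, so no new patients or visits are needed. The downside is that the ranked result is a composite: it partly overlaps with the mRS and cannot be expressed in SF-36 points.
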